## Abstract

**Background:**

The World Health Organization (WHO) launched a Rehabilitation 2030 initiative to call for global action to scale up rehabilitation efforts. Rehabilitation needs are growing, and efforts should be made to strengthen and integrate rehabilitation into all levels of health care, including building research capacity and expanding evidence for rehabilitation. Postdischarge rehabilitation is essential for reducing hospital readmissions and maintaining patients’ health within the community. However, locally, the shift toward community-based rehabilitation is often hampered by long waiting times for admission to day rehabilitation centers (DRCs), cost and logistical barriers, and the lack of a structured program to onboard patients and caregivers to the digital solutions required for rehabilitation in Singapore. Telerehabilitation systems that incorporate wearables within a structured rehabilitation program support inpatient rehabilitation and enable patients to continue with physical rehabilitation after discharge while awaiting admission to a DRC.

**Objective:**

The aim of this randomized controlled trial (RCT) is to investigate the clinical and cost-effectiveness of ATLAS, an AI-assisted telerehabilitation system, among patients admitted to community hospitals (CHs) for rehabilitation.

**Methods:**

This is a 2-arm pragmatic RCT. Participants admitted to CHs for rehabilitation for hip fracture, musculoskeletal conditions, or deconditioning will be enrolled and randomized to either the intervention or control group in a 1:1 ratio. The intervention group, in addition to usual care, will be enrolled in an ATLAS system. The ATLAS system consists of Rebee, an AI-assisted device equipped with a lightweight wireless motion sensor that patients can strap on for real-time feedback and log their exercises via the Rebee application to an electronic platform, as well as a therapist-designed, structured exercise program that patients follow during their inpatient stay and continue upon discharge. The control group will continue to receive usual rehabilitative care in the CHs and upon discharge but will not have access to the ATLAS system. Our primary outcome is functional status. Secondary outcomes include quality of life, length of stay in the CH, 30-day readmission rates, and cost-effectiveness.

**Results:**

A total of 407 participants were recruited between January and September 2025 across 3 CHs, with data collection completed in December 2025. Data analysis is currently underway, and the results are expected to be submitted for publication in Q4 2026.

**Conclusions:**

Our trial will provide valuable insights into the effectiveness and implementation of an AI-assisted telerehabilitation system for patients admitted to the CH for rehabilitation for hip fracture, musculoskeletal conditions, or deconditioning. This trial will also evaluate the sustainability and cost-effectiveness of the ATLAS system, with the potential of scaling across inpatient settings in both acute and CHs.

**Trial Registration:**

ClinicalTrials.gov NCT06683963; https://clinicaltrials.gov/study/NCT06683963

**International Registered Report Identifier (IRRID):**

DERR1-10.2196/78400

## Introduction

The world’s population is aging, and by 2030, 1 in 6 people will be aged ≥60 years [1]. The rapidly ageing population has greatly contributed to the present and future increase in health care costs, with an increase in long-term care expenditures for older individuals [2]. Similarly, in Singapore, the proportion of older adults aged ≥65 years increased from 11.2% in 2014 to 18% in 2024 [3]. In 2017, the World Health Organization (WHO) launched a Rehabilitation 2030 initiative to call for global action to scale up rehabilitation efforts [4]. This initiative recognizes that rehabilitation needs are increasing, and efforts should be made to strengthen and integrate rehabilitation into all levels of health care. This includes building research capacity and expanding evidence for rehabilitation.

Studies have shown that early postdischarge rehabilitation is essential for preventing deterioration, reducing readmissions, and maintaining patients’ health within the community [5-8]. Locally, there have been efforts to improve patients’ access to an expanded scope of community rehabilitation by right-siting suitable patients from acute hospitals and specialist outpatient clinics to community-based rehabilitation facilities, such as day rehabilitation centers (DRCs) [9]. However, the waiting time for DRCs in Singapore can range widely due to limited capacity, alongside other factors, resulting in a median waiting time for day centers of around 20 days [10]. As such, solutions are required that allow for early access to postdischarge rehabilitation, apart from that which is provided by the community rehabilitation facilities.

Besides the availability of community rehabilitation facilities, adherence to postdischarge rehabilitation at these facilities has also been an issue, with postdischarge rehabilitation attendance rates dropping steadily over time [8,11]. The number of rehabilitation sessions attended is closely related to functional outcomes [12]. Barriers to adherence include (1) functional limitations and inconvenience in traveling to rehabilitation centers, (2) caregiver availability, and (3) financial reasons [11,13]. As such, research and development of telerehabilitation has been rapidly expanding to address the above barriers, demonstrating that digital health (DH) care solutions may even perform better than conventional rehabilitation in reducing pain and improving quality of life [14]. Published trials on telerehabilitation have used a combination of methods, ranging from digital devices to home visits and video- or phone-based interventions [15]. However, home-based therapy and traditional telerehabilitation require manpower for visitation and consultation, resulting in additional manpower costs.

The shift toward community-based rehabilitation thus requires a digital solution that should be convenient and most importantly AI-assisted to reduce manpower costs. Studies evaluating unsupervised home exercises via a digital platform or printed programs have been shown to be noninferior to formal outpatient supervised therapy sessions [16-18]. The digital literacy of Singapore’s older adults varies greatly; thus, help is required to smoothen the process of DH adoption and uptake. This will range from providing education on the DH interface and navigation, to ensuring ease of access and support to use of DH devices, recommendations by trusted health care institutions and health care professionals, convenience, provision of free DH devices or monetary incentivization, as well as aligning with participants’ own healthy living goals [19,20].

The Singapore Tele-technology Aided Rehabilitation in Stroke study, which was a randomized controlled trial (RCT) conducted on 124 patients who had a stroke in Singapore, compared a 12-week telerehabilitation system and program to usual care for recent stroke survivors [21,22]. The study demonstrated the feasibility of such self-directed home rehabilitation devices, with similar improvements in functional outcomes noted between both groups. To our knowledge, apart from the above-mentioned study, there are no other clinical trials examining the feasibility, outcomes, and most importantly cost-effectiveness of implementing such self-directed telerehabilitation programs in any other groups of patients in Singapore.

To address this, the team designed the ATLAS study, a 2-arm (intervention-control) RCT conducted across 3 community hospitals (CHs) in Singapore, to evaluate the outcomes and cost-effectiveness of the addition of telerehabilitation systems to usual care, for patients admitted to CHs for rehabilitation for hip fracture, musculoskeletal conditions, or deconditioning. Rebee is a Health Sciences Authority class A certified medical device that has been validated in previous studies locally and abroad for measurement of upper and lower limb range of motion and is approved for clinical trials across the 3 health care clusters in Singapore [23-25]. Rebee consists of a tablet with an attached lightweight wireless motion sensor that patients can strap on for real-time feedback and log their exercises via the Rebee application to an electronic platform that can be viewed by the study team.

Singapore CHs provide postacute care environments characterized by lower levels of anxiety, extended patient stays for rehabilitation, and opportunities for caregiver training [26]. CHs are ideal environments for trials using DH devices, given that patients stay inpatient for up to several weeks for rehabilitation, allowing time for dedicated hospital personnel to familiarize, introduce, and teach patients and their caregivers in the intervention arm how to use DH devices during their stay.

The primary aim of this RCT is to determine if the addition of ATLAS to usual care improves functional status, as compared to usual care alone, in patients admitted to CHs for rehabilitation for hip fracture, musculoskeletal conditions, or deconditioning. The secondary aim is to determine if this also affects patients’ quality of life, length of stay in CHs, 30-day readmission rates, and clinical cost-effectiveness, as compared to usual care alone. The hypothesis is that the addition of ATLAS to usual care improves functional status and quality of life, reduces length of stay in CHs and 30-day readmission rates, and increases clinical cost-effectiveness, as compared to usual care alone. The findings from this study may provide evidence for an enhanced, cost-effective, and sustainable care model for patients admitted for rehabilitation to a CH.

## Methods

### Study Design

This study is an unblinded, multicenter, prospective, pragmatic parallel 2-arm RCT comparing the efficacy and cost-effectiveness of a 12-week application-based telerehabilitation program to usual care across 3 CHs in Singapore. Patients recruited at each site will be randomly allocated in a 1:1 ratio to either an intervention or control group. The intervention group will be enrolled into ATLAS, consisting of a structured exercise program and Rebee, an AI-assisted telerehabilitation device, in addition to usual care. The control group will continue to receive usual care but will not have access to ATLAS (Figure 1). The study design is based on the Pragmatic Explanatory Continuum Indicator Summary Framework-2 (PRECIS-2) [27]. This study protocol is written according to the Standard Protocol Items: Recommendations for Interventional Trials reporting guidelines [28] (Figure 2). Study outcomes will be reported in accordance with the Consolidated Standards of Reporting Trials statement [28].

**Figure 1 figure1:**
[figure not shown]
ATLAS trial workflow.

**Figure 2 figure2:**
[figure not shown]
SPIRIT (Standard Protocol Items: Recommendations for Interventional Trials) checklist for the schedule of enrollment, interventions, and assessments.

### Study Setting

This study was conducted in 3 CHs (Outram Community Hospital, Seng Kang Community Hospital, and Jurong Community Hospital) in Singapore. CHs are purpose-built hospitals that provide medical, nursing, and rehabilitation care for patients who require a short period of care after their stay in the acute hospital before being discharged back to the community [26]. Patients admitted to CHs may come from any acute tertiary hospital in Singapore.

### Ethical Considerations

This study has been approved by the SingHealth Centralised Institutional Review Board (2024-2246) and is registered on ClinicalTrials.gov (NCT06683963). Written informed consent was obtained from all participants before study participation. Participants on each site are assigned a continuous study code to protect identifiable data (eg, OCH001-OCH150, SKCH001-SKCH150, and JCH001-JCH150). The assignment data are kept in a password-protected laptop, within a password-protected document, and only accessible by selected study team members. Participants are compensated for their time and inconvenience via grocery vouchers given upon completion of predefined time points in the study (Singapore $20 [Singapore $1=US $0.77 as of July 21, 2026] before discharge and Singapore $30 at the end of the study).

To ensure confidentiality of participants, only the study team will have access to the research data, both hard and soft copies, at all sites. Rebee Health will only receive deidentified and nonsensitive data. Hard copy data will be stored in designated locked locations (eg, cabinets and rooms) that are accessible to only authorized study personnel. Electronic data will be stored in an institution-approved, secured, and encrypted storage medium, such as databases, encrypted portable media (eg, USB drives, CD or DVD, and hard disks), and/or institution-approved online storage platforms. The electronic data will not contain research participant identifiers. Identification codes linking electronic data and research participants will be stored separately. The research data will be destroyed after they have been stored for the minimum duration of retention as specified by the institutional policy.

### Eligibility Criteria

Patients will be recruited from 3 CHs in Singapore. The inclusion criteria are as follows: (1) age between 21 and 99 years; (2) admission primary rehabilitation diagnostic group (RDG) classified under hip fracture (3.11, 3.12, and 3.13), musculoskeletal conditions (5.11, 5.12, 5.13, and 5.21), or deconditioning (6.1, 6.2, and 6.3) [9]; (3) understand English or Mandarin; and (4) suitable and able to engage in Rebee exercises.

The exclusion criteria are as follows: (1) colonized by multi-drug-resistant organism; (2) presence of neuropsychiatric or neurocognitive disease affecting the ability to follow instructions; (3) unable to full weight bear, or restrictions to range of motion; and (4) refusal to participate or give informed consent.

### Usual Care

Patients admitted to CHs undergo inpatient rehabilitation for around 3 to 4 weeks before being discharged home. During the CH admission, participants in both arms will receive standardized CH rehabilitation comprising both physiotherapy and occupational therapy sessions. Physiotherapy and occupational therapy sessions are each held for 30 to 60 minutes per session, up to 5 times a week, covering a range of items including warm-up, strength training, cardiovascular training, and balance training. All training may be conducted in either a group or one-to-one setting based on clinical needs and patient safety considerations [26]. Caregiver training is provided to patients and their respective family members or caregivers as needed prior to discharge.

All therapists delivering rehabilitation services are registered under the Allied Health Professions Council, a professional board that is governed and regulated by the Ministry of Health. This ensures standardization of professional qualifications across both study arms.

After discharge from a CH, participants will be referred to outpatient rehabilitation facilities as recommended by the CH team (eg, center-based therapy at DRCs or outpatient therapy clinic, or home-based therapy) as per usual care. They will be prescribed exercises communicated via printed materials, verbal instruction, and demonstration.

### Intervention

During their CH stay, patients in the intervention arm will be enrolled in the ATLAS program in addition to usual care (Figure 1). The ATLAS program is provided free of charge to the patients and their caregivers, with follow-up and support provided during their stay as well as upon discharge for up to 12 weeks. It consists of Rebee, an AI-assisted telerehabilitation device with a wearable sensor, and a structured rehabilitation program.

#### Rebee

Participants in the intervention arm will be provided a tablet containing the Rebee application and a linked wearable sensor (Figure 3). The Rebee interface is simple and intuitive to use, with video demonstrations on how to perform the exercises and a virtual 3D avatar that translates movements detected by the linked sensor into visual and audio cues to provide real-time feedback and gamification of exercises (Figure 4).

**Figure 3 figure3:**
[figure not shown]
Wearable sensor, Rebee application, and therapist web portal. More information can be found on the Rebee Health website.

**Figure 4 figure4:**
[figure not shown]
Rebee virtual 3D avatar with real-time tracking and feedback of movements and range.

As Rebee’s clinical platform has been whitelisted in SingHealth and National University Health System, study team members will be able to access the Rebee therapist web portal from their corporate devices to access and monitor participants’ progress.

#### Structured Program

Upon recruitment, the study team will upload a set of inpatient rehabilitation exercises to the Rebee portal, with the type of exercise, number of sets, and number of repetitions predetermined according to the participant’s RDG grouping (Tables 1 and 2). These exercises were decided upon via consensus by the lead therapists in the study team across all 3 CH sites, modeled after deemed safe for patients to perform on their own without supervision from the inpatient rehabilitation team. The study team will then visit the participant daily to provide guidance and training on the use of the Rebee device, until the participant and/or their caregivers are deemed competent to use the device on their own. Participants will be provided phone numbers to contact the study team if they have issues or questions.

**Table 1 table1:** List of inpatient exercises.

TKR^a^	All others^b^
Isometric quads (ISO knee extension; 2 sets × 5 reps, ISO 5 s hold)	Bridging (2 sets × 5 reps)
Single-leg raise with towel (2 sets × 5 reps, ISO 5 s hold)	Supine heel slide (left and right; 2 sets × 5 reps)
Passive knee flexion with towel (2 sets × 5 reps, ISO 5 s hold)	Supine hip abduction (left and right; 2 sets × 5 reps)
Seated knee extension (2 sets × 5 reps, ISO 5 s hold)	Single-leg raise (left and right; 2 sets × 5 reps)
Seated marching (3 sets × 1 min, 30 s rest in between)	Seated knee extension (left and right; 2 sets × 5 reps, ISO 5 s hold)

^a^TKR: total knee replacement.

^b^This includes all participants under rehabilitation diagnostic group hip fracture (3.11, 3.12, and 3.13), musculoskeletal conditions (5.11, 5.12, and 5.21), and deconditioning (6.1, 6.2, and 6.3), except for total knee replacement (5.13).

**Table 2 table2:** List of outpatient exercises.

TKR^a^	All others^a^
Isometric quads (ISO knee extension; 3 sets × 10 reps, ISO 5 s hold)	Bridging (2 sets × 10 reps)
Single-leg raise with towel (3 sets × 10 reps, ISO 5 s hold)	Supine heel slide (left and right; 2 sets × 10 reps)
Passive knee flexion with towel (3 sets × 10 reps, ISO 5 s hold)	Supine hip abduction (left and right; 2 sets × 10 reps)
Seated knee extension (3 sets × 10 reps, ISO 5 s hold)	Single-leg raise (left and right; 2 sets × 10 reps)
Brisk marching on the spot (3 sets × 1 min, 30 s rest in between)	Seated knee extension (left and right; 2 sets × 10 reps, ISO 5 s hold)

^a^TKR: total knee replacement.

^b^This includes all participants under rehabilitation diagnostic group hip fracture (3.11, 3.12, and 3.13), musculoskeletal conditions (5.11, 5.12, and 5.21), and deconditioning (6.1, 6.2, and 6.3), except for total knee replacement (5.13).

Participants are to follow and perform the preset exercises on the Rebee device in their own time, in addition to routine rehabilitation sessions conducted during their stay in the CHs. Upon discharge, the preset exercises will be updated to an outpatient regime (Table 2), and participants will be advised to continue performing these exercises on their own.

Study team members will check in with the participants if the Rebee device has not been used for 3 or more consecutive days to troubleshoot or understand reasons for lack of use. Participants are allowed to discontinue the Rebee device upon request, and reasons for such discontinuation are recorded (eg, not interested anymore and unable to continue using the Rebee device due to reasons such as injury, admission to hospital, or travel). The Rebee device will be retrieved at the end of the study at week 12 through a scheduled home visit.

### Outcome Measures

The primary outcome is functional status measured over 12 weeks. Functional status will be measured using modified Barthel index (MBI), a 100-point ordinal scale for the assessment of a patient’s functional state. The MBI assesses activities of daily living over 10 domains comprising transfers, ambulation, stair climbing, bathing, dressing, toileting, bowel control, bladder control, personal hygiene, and feeding [29].

Secondary outcomes include physical performance, quality of life, length of stay in CH, 30-day readmission rates, and cost-effectiveness over 12 weeks. Patients who are admitted under RDG total knee replacement will have an additional outcome measure of joint range. The outcome measures as well as the method of measurement are listed in Table 3. Health care cost will be calculated from electronic medical records and supplemented with survey data regarding the number of DRC or home therapy sessions attended, manpower hours to train patients to use Rebee, costs of Rebee software and hardware, and use of outpatient community services (eg, day care center, home nursing, housekeeping, and meals on wheels). The tools to be used in this study to measure the outcomes are validated and implemented in routine clinical care.

**Table 3 table3:** Primary and secondary outcome measures.

Variables			Data source, method of measurement, and definitions		Time points
Primary outcome					
	Functional status	Survey: MBI^a^. To establish the degree of independence from any help. A score from 0- 100 using the MBI questionnaire, with 100 being fully ambulant without any help.		Baseline and 4, 8, and 12 weeks	
Secondary outcomes					
	Joint range	Measurement using goniometer on affected knee. Active and passive range of motion (flexion and extension) of affected knee.		Baseline and 4, 8, and 12 weeks	
	Physical performance	Measured by performing 5CST^b^. Measures the time taken to complete 5 sit to stands (in seconds)		Baseline and 4, 8, and 12 weeks	
	Quality of Life	Survey: EQ-5D-5L		Baseline and 4, 8, and 12 weeks	
	Length of stay	Electronic medical records		Date of discharge from CH^c^ minus date of randomization	
	30-day readmission rates	Electronic medical records		12 weeks	
	Direct health care cost	Electronic medical records: cost of inpatient stay		12 weeks	
	Direct health care cost	CRC’s^d^ daily expenditure of manpower		4, 8, and 12 weeks	
	Direct health care cost	Rebee costs: software and hardware		12 weeks	

^a^MBI: modified Barthel index.

^b^5CST: 5-time chair stand test.

^c^CH: community hospital.

^d^CRC: clinical research coordinator.

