### Randomization and Blinding

Participants will be randomized to the intervention or control group based on a 1:1 allocation ratio. Stratified block randomization with randomly varying block sizes will be implemented with recruitment site as the stratification factor.

After taking informed consent, the research coordinator will contact a member of the team (who oversees the progress but is not involved in patient recruitment) to obtain the randomized assignment. The research coordinator will remain blinded to the allocation prior to contacting the team member. Due to the nature of the intervention, blinding of study participants will not be possible.

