The preferred method of imputation will be applied accordingly based on the degree of missingness, such as last observation carried forward.

The cost-effective analysis will evaluate both direct cost savings and cost-effectiveness in terms of quality-adjusted life years (QALYs). To assess direct cost savings, the analysis will evaluate the difference in length of stay at the hospital between the intervention and control group (Table 4). The results will be expressed as mean cost differences between groups. Cost per QALY gained will be evaluated for the cost-effectiveness of the intervention. QALY will be derived using EQ-5D-5L utility scores, and incremental cost-effectiveness ratios (ICERs) will be calculated. The ICERs will be compared to established willingness-to-pay thresholds to determine the cost-effectiveness of the intervention. Sensitivity analyses will be performed to account for uncertainties in cost and QALY estimates. Results will be presented using cost-effectiveness planes and acceptability curve.

**Table 4 table4:** Cost-accounting for the cost-effectiveness analysisa.

Cost category	Cost type	Cost item	Unit of measurement	Source of unit cost	Applicable to
Hardware	Direct	Rebee kits	Per kit per day	Research collaboration agreement	Intervention
Software	Direct	Rebee subscription	Per patient per day	Research collaboration agreement	Intervention
Inpatient care	Direct	Average length of stay	Per patient per day	Electronic medical records	Control and intervention
Manpower	Direct	CRC’s^b^ daily EOM^c^	Per day	Human resource	Intervention

^a^The statistical analysis will be conducted using R (R Foundation for Statistical Computing). All evaluations will be made using 2-side *P* values at the 5% level of significance.

^b^CRC: clinical research coordinator.

^c^EOM: expenditure of manpower.

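### Staff input is costed as device-training hours in the text but as a research coordinator's daily expenditure in Tables 3 and 4, which can put trial work into the intervention's cost

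*Protocol article*

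**What the plan says.** The protocol article describes the staff cost in three places.

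- **Outcome Measures, text.** Among the inputs that supplement the medical records is "manpower hours to train patients to use Rebee". The quantity is hours and the activity is device training.
- **Outcome Measures, Table 3.** One of the direct health care cost rows is the CRC's "daily expenditure of manpower", recorded at 4, 8 and 12 weeks. The footnote reads "CRC: clinical research coordinator". Training hours do not appear in the table, and the table has no column for study arm.
- **Statistical Analyses, Table 4.** The manpower row is the CRC's daily EOM ("EOM: expenditure of manpower"). The unit is a day, the unit cost comes from human resources, and the row applies to the intervention arm only.

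Two other sections show what the staff do. Under Structured Program, "The study team will then visit the participant daily to provide guidance and training on the use of the Rebee device" until the participant or caregiver is competent, and later "Study team members will check in with the participants if the Rebee device has not been used for 3 or more consecutive days". Under Randomization and Blinding, "After taking informed consent, the research coordinator will contact a member of the team" to obtain the assignment.

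The costs feed the economic result directly: under Statistical Analyses, "incremental cost-effectiveness ratios (ICERs) will be calculated" on QALYs derived from the EQ-5D-5L.

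**The concern.** The same cost item is described in two ways that differ in unit and possibly in scope. Hours of device training are a measure of what it takes to deliver the intervention. A coordinator's daily expenditure is a measure of what it takes to employ someone who also runs the trial. Obtaining allocations serves both arms and would not exist in routine use. If coordinator days are charged to one arm without separating the tasks, part of the cost of doing the research is counted as a cost of ATLAS.

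Table 4 has four cost rows, three of which apply to the intervention only, so manpower is a direct part of the incremental cost. The Introduction justifies an AI-assisted solution by its saving in manpower, and Future Directions offers the results to policymakers. An error in the staff line would therefore bear on a main message of the economic evaluation. The limitations section discusses only underestimation of costs, from omitted postdischarge services and readmissions. It does not consider overstatement from research time.

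**Working it through.** The article states no staff cost, wage, number of hours or number of coordinator days, so there is no figure to reproduce. The check is a comparison of the passages, followed by two illustrations on assumed inputs.

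**1. Unit.** The text counts hours and Table 4 counts days. No sentence or footnote converts one to the other.

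**2. Denominator.** In Table 4 the hardware row is per kit per day, and the subscription and inpatient rows are per patient per day. The manpower row is per day alone. As written, it gives no means of sharing a coordinator's day among patients, arms or tasks.

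**3. Scope.** Device training takes place by daily visits during the community hospital stay, which Usual Care puts at around 3 to 4 weeks. Table 3 records the coordinator's expenditure at 4, 8 and 12 weeks, so it appears to reach beyond training. Some of the later work belongs to the intervention: updating the exercises at discharge, check-ins for non-use and the home visit to retrieve the device. The text's item, training alone, would leave these out.

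**4. Tasks of the role.** Taking the research coordinator named under Randomization and Blinding to be the clinical research coordinator of Tables 3 and 4, the role includes obtaining the allocation after consent for every participant. That is trial work in both arms. The article does not say who measures the outcomes.

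**5. Illustration of the day unit.** Assume an 8-hour day and *h* hours of device work for one intervention patient, with the whole day charged to that patient. The overstatement factor for that day is 8/*h*:

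- *h* = 0.5: 8/0.5 = 16
- *h* = 1: 8/1 = 8
- *h* = 2: 8/2 = 4
- *h* = 4: 8/4 = 2
- *h* = 8: 8/8 = 1

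If the day is shared by *k* intervention patients with *h* hours each, the factor is 8/(*k* × *h*). With *h* = 1 it is 2 for *k* = 4 and 1 for *k* = 8. If daily EOM is only a rate applied to recorded device time, the factor is 1.

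**6. Illustration of the effect on the ICER.** QALY gain = utility gain × 12/52, for a gain assumed to be held in full over 12 weeks. The change in the ICER per misallocated S$100 per patient is 100 divided by the QALY gain:

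- gain 0.03: 0.03 × 12/52 = 0.0069 QALY; about S$14,400 per QALY
- gain 0.05: 0.05 × 12/52 = 0.0115 QALY; about S$8,700 per QALY
- gain 0.08: 0.08 × 12/52 = 0.0185 QALY; about S$5,400 per QALY

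The S$100 and the three utility gains are assumptions. The figures show how sensitive the ratio is to any cost line over a 12-week horizon. They do not estimate the bias in this trial.

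**The case against.** The strongest reply is that hours and daily EOM are a quantity and a price. Table 4 has a column for the source of unit cost, and for manpower it names human resources, which fits a pay rate used to value recorded training time. The restriction to the intervention arm also fits the view that only device-related work is counted, since consent and randomization occur in both arms. On that reading nothing is overstated. This reply stands in part. A reader might infer from Table 4 that research work is in fact loaded into the ICER, but the article does not support that: nowhere does it say that consent, randomization or assessment time enters the daily figure. The reply does not remove the conflict, because the same table gives the unit of measurement as a day without a patient denominator, and the text gives hours.

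A second reply is that much of the study team's work is a true delivery cost, so counting training hours alone could understate it. This is right, and the fix below is worded accordingly.

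A third is that sensitivity analyses on costs are already planned, and that a condensed article may leave the costing rule to a fuller document. General sensitivity analyses vary the estimates; they do not settle which time is costed. And the issue is not an omitted detail: the article specifies the item more than once, and the specifications differ.

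A fourth is that the hypothesis includes a shorter stay, so the net incremental cost could be negative. That is also right. An overcharge would then shrink an apparent saving, so it would still work against the intervention.

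**Conclusion.** The inconsistency is real. The text costs hours of device training, Tables 3 and 4 cost the coordinator's daily expenditure, and Table 4 charges it per day, unapportioned, to the intervention arm. Only Table 4 assigns an arm. Because the coordinator also does trial work for both arms, a literal application of Table 4 can place research time in the incremental cost and, given a QALY gain, bias the ICER upward.

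That is a risk created by the wording, not a demonstrated bias. Its size cannot be determined from the documents, and it is nil if daily EOM is simply a rate applied to recorded device time. The multipliers and the S$ per QALY figures rest wholly on assumed inputs and should not be read as the effect in this trial, or as showing that the conclusion on cost-effectiveness would change. The point concerns a secondary outcome, but one that carries the case for scale-up, so it should be settled before the economic analysis is reported.

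**What to change.** Reconcile the Outcome Measures text with Tables 3 and 4 under one costing rule:

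- Cost the recorded staff time for delivering ATLAS per intervention patient: uploading and updating the exercises, device training, troubleshooting, check-ins for non-use, and retrieval of the device.
- Value that time at the human resources rate converted to an hourly figure, and state the conversion.
- Exclude time spent on consent, randomization and outcome assessment.
- Show the full daily-EOM version as a sensitivity analysis.

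The cost is a change of wording in the text, the two tables and the analysis plan. Training hours are already listed as an input, and the article reports that the analysis is still underway. The downside is that some hours, especially for tasks other than training, may not have been logged. In that case a sampled average per patient, with a range, would be needed and should be reported as such.
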